## 11. Outcome measurement

### A. Questionnaire and interview

Participants in the intervention and control groups will be interviewed by the researchers at the time of enrollment. Additionally, they will be assessed using a questionnaire at the time of enrollment, three months, and six months. The questionnaire will be administered when the patients and caregivers will visit the institutions for outpatient treatment or hospitalization within one month before or after the time of enrollment. The research nurse will visit the outpatient or inpatient ward to directly evaluate the patients. If the patient and guardian do not visit the hospital due to the absence of outpatient or hospitalization schedules within one month before or after the time of enrollment, the nurse will contact the patient and guardian by phone or email to complete the questionnaire.

| Item | Enrollment | 3m | 6m | 12m | Evaluation Method |
|------|------------|----|----|-----|-------------------|
|------|------------|----|----|-----|-------------------|

|                                                                                                                                                                                                                                                                                                                                                                                                                                                       |   |   |    |   |                                               |
|-------------------------------------------------------------------------------------------------------------------------------------------------------------------------------------------------------------------------------------------------------------------------------------------------------------------------------------------------------------------------------------------------------------------------------------------------------|---|---|----|---|-----------------------------------------------|
| Demographic characteristics
Patient: age, sex, residence, medical security, education, marital status, religion, employment, monthly income, welfare service, disability type, private insurance, household characteristics, family and household composition, care provision status
Guardian: age, sex, relationship with the patient, co-residence with the patient, education, marital status, religion, employment, patient care experience | ⊙ | ⊙ | ⊙  | ⊙ | Researcher interview
Patient questionnaire |
| Patient's general condition.                                                                                                                                                                                                                                                                                                                                                                                                                          | ⊙ | ⊙ | ⊙  | ⊙ | Researcher interview                          |
| Medical equipment in possession                                                                                                                                                                                                                                                                                                                                                                                                                       | ⊙ |   |    |   | Researcher interview                          |
| Symptoms and dietary intake                                                                                                                                                                                                                                                                                                                                                                                                                           | ● |   |    |   |                                               |
| Drug evaluation                                                                                                                                                                                                                                                                                                                                                                                                                                       | ● |   |    |   |                                               |
| Patient's quality of life (EQ-5D)                                                                                                                                                                                                                                                                                                                                                                                                                     | ⊙ | ⊙ | ●  |   | Patient questionnaire                         |
| Patient's symptoms (ESAS)                                                                                                                                                                                                                                                                                                                                                                                                                             | ⊙ | ⊙ | ●  |   | Patient questionnaire                         |
| Patient's emotional status (PHQ-9)                                                                                                                                                                                                                                                                                                                                                                                                                    | ⊙ | ⊙ | ●  |   | Patient questionnaire                         |
| Patient's satisfaction with the service                                                                                                                                                                                                                                                                                                                                                                                                               |   | ● | ●  |   | Patient questionnaire                         |
| Caregiver's quality of life (EQ-5D)                                                                                                                                                                                                                                                                                                                                                                                                                   | ⊙ | ⊙ | ●  |   | Patient questionnaire                         |
| Caregiver's emotional status (PHQ-9)                                                                                                                                                                                                                                                                                                                                                                                                                  | ⊙ | ⊙ | ●  |   | Patient questionnaire                         |
| Caregiver's burden of care (CRA-K)                                                                                                                                                                                                                                                                                                                                                                                                                    | ⊙ | ⊙ | ●  |   | Patient questionnaire                         |
| Caregiver's preparation for care                                                                                                                                                                                                                                                                                                                                                                                                                      | ⊙ | ⊙ | ●  |   |                                               |
| Caregiver's competence                                                                                                                                                                                                                                                                                                                                                                                                                                | ⊙ | ⊙ | ●  |   |                                               |
| Caregiver's sense of accomplishment for care                                                                                                                                                                                                                                                                                                                                                                                                          | ⊙ | ⊙ | ●  |   |                                               |
| Caregiver's satisfaction with the service                                                                                                                                                                                                                                                                                                                                                                                                             |   | ● | ●  |   | Patient questionnaire                         |
| Caregiver's indirect medical expenses                                                                                                                                                                                                                                                                                                                                                                                                                 |   | ⊙ | ⊙* |   | Patient questionnaire                         |

⊙ Both intervention/control groups, ● Only intervention group

\*Conducted in the control group only when consent is provided at 3 months after enrollment for evaluation at 6 months.

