| Procedures          | 
1. Participant Recruitment
 
 
- Post the essential information in the outpatient and inpatient wards and public bulletin boards of the participating institutions. Explain the study to the patients and their guardians who meet the inclusion criteria in the outpatient or inpatient ward of co-researchers and register consenting individuals.
 
 
2. Clinical Trial
 
1) The Intervention Group (HBMC provided)
 
 
- The HBMC teams of institutions that will provide the intervention will include physicians, nurses, and social workers. Physicians and social workers involved in the existing patients' treatment and consultation can concurrently serve on the HBMC team, and nurses will be dedicated to home care.
 
- For inpatients, a HBMC team nurse will conduct the initial assessment, provide home care educational materials, and conduct home care education within a week before the scheduled discharge date. In the case of outpatients, the initial evaluation, provision of home care educational materials, and home care education will be conducted by a HBMC team nurse on the day of the outpatient visit.
 
- Within two weeks of enrollment in the study, a HBMC team medical staff (e.g., physicians and nurses) will visit the patient's home to assess their home care environment and educate them on the requirements for an appropriate home-care environment. The home care education will include education on taking medications, possible symptoms, and establishing care goals.
 
- The HBMC team will conduct monthly multidisciplinary meetings to share information on patients in the HBMC group and modify the home care management plan through periodic reevaluations.
 
- After the first home visit, the HBMC team nurse will check the patient's home care management status by contacting the patient and their guardian via phone call or text message every two weeks. The HBMC team physicians will be notified about the changes in patients' symptoms, and the medications, outpatient visits, and hospitalization schedules will be modified accordingly.
 
- Patients receiving the HBMC will be provided with a phone number reachable between 09:00 AM and 05:00 PM. This number will be operated by a nurse on the HBMC team who will provide the required consultation and education.
 
- Patients would be allowed to use other medical services, such as existing hospitalization, outpatient visit, ER visit, home care, and visit to a medical institution in the community as before.
 
 
2) The Control Group
 
 
- A research nurse will provide home care educational materials to patients who have consented to participate in the study one week before their discharge in the case of inpatients and on the day of the outpatient visit for outpatients.
 
- The patients can continue using the existing inpatient, outpatient, ER, home care, and community medical institution services other than the HBMC.
 
 
3) Analysis Methods
 
 
- Patients in the intervention and control groups will be followed up, after which a comparative analysis of the outcome variables will be performed.
 
 |

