| Efficacy Assessment | 
1. Data Collection
 
1) Questionnaire
 
 
- Patients and guardians in both the intervention and control groups will complete a questionnaire at the time of participant registration.
 
- Participants in the intervention and control groups will complete a follow-up questionnaire 3 months after registration.
 
- Participants in the intervention group will complete an additional questionnaire 6 months after registration. In the case of the control group, only those who will provide consent to participate in the additional questionnaire at 3 months will complete the additional questionnaire at 6 months.
 
 
2) Medical Records Investigation
 
 
- Medical records at medical institutions will be investigated at 3, 6, and 12 months after the patient's registration for hospitalization (number and dates of hospitalizations), critical care use (date of ICU admission, date of ventilator support, and number of CPR attempts), and emergency room use (number of emergency room visits) at each time point.
 
- In the case of death at 3, 6, and 12 months after registration, the deceased patient's use of medical services (hospitalization, critical care use, and emergency room use) within one month of their death will be investigated.
 
 
3) Secondary Data Linkage
 
 
- For patients who will provide consent to secondary data linkages, the hospitalizations, medical expenses, death, type of end-of-life medical services used, and the use of emergency room, critical care, and hospice between the time of registration and 12 months will be investigated when all patients have been enrolled for 12 months or longer.
 
- Death, information related to hospice use, and the type of end-of-life medical services used will be investigated when all patients have been enrolled for 18 months or longer.
 
- For patients who will consent to secondary data linkages, whether legal forms for life-sustaining treatments (e.g., advance directives and physician orders for life-sustaining treatment) have been completed and by whom will be investigated at 12 and 18 months of enrollment when all patients have been enrolled for 12 and 18 months or longer, respectively.
 
 |

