### ***3) Home visits by nurses***

Nurses in the team will visit the enrolled patient's home within 2 weeks of the initial

assessment. They will make an appointment for a home visit when both the patient and their family caregiver are available. Next, they will assess the home environment for the patient's care, medication, and medical device management. Patients will be educated regarding the condition of their home environment, fall prevention, symptom management, medication counseling, medical device management, and critical symptoms that need to be reported to nurses.

- The medical staff on the HBMC team will evaluate the following items at patients' homes.

| Category                         | Content                                                                                                                                                   |
|----------------------------------|-----------------------------------------------------------------------------------------------------------------------------------------------------------|
| Home Care Environment            | Risk factors in patients' homes (e.g., rooms, living rooms, and bathrooms); potential risk of falls; proper management of medications and medical devices |
| Medication Administration        | Types of medication a patient has or is currently taking along with the medications prescribed by the institution and the methods of administration       |
| Medical Device Management Status | Whether patients are using medical devices appropriately at home in case they possess a device                                                            |
| Symptoms and Dietary Intake      | Assess the symptoms reported by the patient and their dietary intake                                                                                      |
| Performance Status               | ECOG performance status, CFS score                                                                                                                        |
| Vital Signs                      | Assessment of blood pressure, pulse rate, respiratory rate, body temperature, and oxygen saturation after the registration at the first visit             |

- The medical staff on the HBMC team will evaluate the following items at patients' homes. If adjustments to the home care environment besides the content covered in the initial training are necessary, then education on the relevant content will be provided.

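### Section 11.A sets the questionnaire window at one month either side of enrolment, which contradicts the rest of the protocol and permits a baseline taken after HBMC has begun

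*Protocol*

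**What the plan says.** The protocol times the enrolment questionnaire in more than one way.

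- **Section 11.A, Questionnaire and interview.** Participants in both arms are interviewed at enrolment, and "they will be assessed using a questionnaire at the time of enrollment, three months, and six months". The next sentence places administration at a visit for "outpatient treatment or hospitalization within one month before or after the time of enrollment". If there is no such visit, "the nurse will contact the patient and guardian by phone or email to complete the questionnaire". The fallback repeats the enrolment anchor and gives no latest date.
- **Overview, Efficacy Assessment.** Patients and guardians in both arms "will complete a questionnaire at the time of participant registration". No window is given.
- **Sections 9.A.2 and 9.B.2.** An initial assessment covering quality of life, symptoms, mood and caregiving load takes place at enrolment, again without a window.

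The intervention starts early. In the Overview (Procedures), outpatient "home care education will be conducted by a HBMC team nurse on the day of the outpatient visit"; for inpatients the team nurse is to "conduct home care education within a week before the scheduled discharge date". The first home visit is timed from enrolment in the Overview ("Within two weeks of enrollment in the study, a HBMC team medical staff") and from the initial assessment in section 9.B.3 ("Nurses in the team will visit the enrolled patient's home within 2 weeks of the initial", the next word being assessment). Contact every two weeks follows. Controls receive educational materials and usual oncology care, with no home visits or biweekly calls.

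The Overview (Statistical Analysis) states that the regression models will adjust for baseline differences between the arms.

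**The concern.** A baseline should be measured before treatment can influence it. Section 11.A does not require this. It allows the enrolment questionnaire to fall up to a month after enrolment, when home visits and calls may already have begun in the intervention arm and have no counterpart in the control arm. Allocation is by institution and not randomised, so the analysis depends on adjusting for baseline differences. If the scores used for that adjustment already carry some of the intervention's effect, the adjustment subtracts it.

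The wording has two further consequences. The earlier half of the window allows completion before enrolment, which sits badly with section 16.A.3, where consent must come before any trial procedure. And because the window is tied to enrolment, the 3- and 6-month questionnaires have no usable window.

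The outcomes at stake are those measured at enrolment and again later: EQ-5D and PHQ-9 for patient and caregiver, ESAS for the patient, and CRA-K and the caregiver preparation, competence and accomplishment scales.

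**Working it through.** The protocol states no figure that needs reproducing here. The check sets the calendars side by side and then shows, on assumed values, what a late baseline could do.

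**Step 1: overlap of the windows** (day 0 = enrolment)

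| Event | Timing | Source |
|---|---|---|
| Questionnaire window under 11.A | day -28/31 to day +28/31 | section 11.A, one month each side |
| HBMC education, outpatients | about day 0 | Overview, Procedures |
| HBMC education, inpatients | in the week before planned discharge | Overview, Procedures |
| First home visit | day 14 at the latest | Overview, Procedures |
| First biweekly contact | day 14 + 14 = day 28 if the visit is on day 14 | Overview, Procedures |

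- Days of the post-enrolment half that follow a home visit made on the last permitted day: 28 - 14 = 14, or 31 - 14 = 17.
- As a share of that half: 14/28 = 50%, or 17/31 = 55%. An earlier visit raises the share.
- The first biweekly contact, on day 28 or sooner if the visit is made on time, also falls inside the window.
- For outpatients, nearly all of the post-enrolment half can follow the education given at about day 0.

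**Step 2: does another reading remove the problem?** Suppose the sentence was meant as one month around each scheduled time point. Enrolment is one of the three points listed in 11.A, so the enrolment questionnaire could still be a month late. Only a reading that confines the window to months 3 and 6 removes the problem, and the printed text does not say that.

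**Step 3: which comparison is exposed.** The 11.A schedule marks EQ-5D, ESAS, PHQ-9 and the caregiver scales at 6 months as intervention-only. The Overview makes the control arm's 6-month questionnaire depend on extra consent. Month 3 is therefore the main complete between-arm comparison, and a baseline one month late uses up to one third of that interval.

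**Step 4: illustration on assumed values.** Let q be the share of intervention patients with a late baseline, f the fraction of the month-3 effect already present in that late score, and b the slope of the follow-up score on baseline. The protocol gives none of these.

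- Baseline score as covariate: fraction of the effect kept = 1 - b·q·f. With b = 0.5: 1 - 0.5 × 0.25 × 0.25 = 97% (q = 0.25, f = 0.25), down to 1 - 0.5 × 1 × 0.5 = 75% (q = 1, f = 0.5).
- Change score (not planned in the protocol; shown as a bound): 1 - q·f, that is 94% down to 50% for the same pairs.
- Baseline score not used: nothing is lost.

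**The case against.** The strongest reply is that the sentence is a drafting or translation slip meant for follow-up. Patients are recruited and consented in the clinic or ward, so a fallback for people with no hospital visit has little purpose at enrolment and makes sense at months 3 and 6. The initial assessment is already set at enrolment, the Overview lists it ahead of the materials and education, and section 9.B.3 times the home visit from it. Much of this stands: a slip is plausible, and the missing window for months 3 and 6 comes from the same wording and is not a separate defect. It does not clear the text. The anchor is printed twice, the Overview times the visit from enrolment, and no passage states that the initial assessment and the questionnaire are the same thing.

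A reader might infer more than the protocol supports:

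- *That all reported outcomes are biased.* Patient and caregiver satisfaction and indirect expenses have no enrolment measurement. Unscheduled hospitalisation, the primary endpoint, comes from records and linked data.
- *That a change-score effect is diluted.* No change score is planned. Sections 12.B and 14 compare group means, and an unadjusted month-3 comparison does not depend on baseline timing. The adjustment in the Overview does not name the baseline questionnaire scores as covariates.
- *That only the intervention arm is exposed to anything at enrolment.* Controls also receive materials, and the one-to-one session in section 9.A.2 sits in the general enrolment section. The clear difference between arms is the home visits and calls.
- *That baselines will usually be late.* The protocol gives no frequency, and recruitment at hospital visits makes completion at enrolment practicable.

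**Conclusion.** The point holds as an inconsistency that should be corrected. Section 11.A conflicts with the Overview and sections 9.A.2 and 9.B.2 on when the enrolment questionnaire is completed. Followed as printed, it permits a baseline taken after the intervention has begun, and it leaves months 3 and 6 without a usable window.

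The overlap is firm on the protocol's own timings, taking a month as 28 to 31 days: at least half of the post-enrolment window falls after a home visit made on time. The effect on results is conditional. It arises only if some baselines are in fact late, the early contacts move the scores, and those scores enter the baseline correction. On the assumed values above, adjustment would keep about 75% to 97% of the effect on the affected secondary outcomes. The range is illustrative and not an estimate for this trial. The conclusion on the primary endpoint is not directly affected.

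The matter deserves more than a note on wording, because the design relies on baseline adjustment and no later analysis can recover a baseline that was not taken in time.

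**What to change.** In section 11.A:

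1. Require the enrolment questionnaire at registration, after consent and before any HBMC education or home visit.
2. Attach the one-month window, before or after, to the 3- and 6-month time points only. Tie the phone and email fallback to the same points and give it a latest date.
3. Record the completion date of every questionnaire.

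The cost is a few lines in 11.A and one date field per questionnaire. The change agrees with the Overview, with the initial assessment in section 9 and with the consent requirement in section 16.A.3. If questionnaires have already been collected under the printed rule, comparing completion dates with the dates of education and first home visit would show how many baselines were late.
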